#### Interviews

Participant preference for comfort and safety and maintaining confidentiality will be our guiding principle. Interviews will take place where they cannot be overheard and the interviewer will confirm that the participant is happy to proceed at the time and location before commencing the interview. If the situation changes, people move nearby, or the interviewee appears uncomfortable then the interviewer will pause, stop, or rearrange the interview as necessary. Participants will be informed during the consent procedure, and at the end of the interview, that if they feel they would like to talk to a counsellor about something that has come up during the interview then we can refer them to local services for support.

We plan to reimburse participants for their time spent participating in the research, with additional costs given for travel. On the advice of community advisory groups, reimbursements will be a product such as a bar of soap and/or notebook. Some additional qualitative activities, such as walking through communities and other participant-observation, will not usually require reimbursement.

### Strategies to minimise attrition between waves 2 and 3

At Wave 2 contact, for those who consent to cohort enrolment, we will record a set of detailed contact information. This will include: GPS location of the participants’ residence if they interviewed where they reside; mobile phone number if they have a phone or have access to a phone; social media contacts; contact mobile phone numbers and social media contacts of up to 3 caregivers, relatives, or others who are likely to be informed of the index adolescent’s whereabouts. Participants will be asked to nominate one of these as a ‘link person’.

We will maintain regular contact with participants and/or their given link person. We expect this will comprise of phone contact at least every 6 months, and every 3 months over key transition periods, when we know schooling is ending or a job is beginning. We will provide a toll free phone number that will appear on their ID card and encouragement to call and let us know if they are moving or their contact information is changing. We are also exploring the use of social media to facilitate ongoing contact, and will seek advice from our collaborator groups (for example, we may set up a study Facebook page if collaborators feel this would be useful and privacy can be maintained).

For those participants who are additionally engaged in the qualitative component, phone contact at least every 6 months, and every 3 months over key transition periods will supplement the multiple contacts during annual data collection periods.

### Measures for the quantitative survey

Measures in the Wave 2 survey will be a combination of measures used in our Wave 1 survey with 11–14 year olds, a further survey we have more recently conducted with 500 adolescents attending secondary school in Kampala as part of the Good School Toolkit secondary school adaptation research, and measures adapted from existing studies, which we will pre-test. In some cases we will develop simple sets of items and pre-test these. The final Wave 2 questionnaire will be pilot tested for overall length and flow, and the number of questions asked will be reduced such that overall completion time is not more than approximately one hour.

Measures are mainly from internationally recognised tools, and include: background socio-demographic information, disability (using the Washington Group Short Set of questions [26]), family and peer and school connectedness (from the Minnesota Student survey and Add Health [27]), adolescent risk and sexual behaviours (from Global School Health Surveys, the Health Behaviour in School Aged Children Surveys, National Survey of Sexual Attitudes and Lifestyles), including alcohol use (sub-set of questions from AUDIT [28]) and exposure to the Good School Toolkit intervention (developed from Good School Study [29]), previous disclosures of violence (from Good School Study), questions about paid and unpaid work (from the Good Schools Study). A summary of the main violence and mental health outcome measures are provided in Table 1.

**Table 1 Tab1:** Summary of main violence and mental health outcome measures

Area	Source of questions
Violence from school staff against students	Adapted from International Society for the Prevention of Child Abuse and Neglect-Child Abuse Screening Tool-Child Institutional, ICAST-CI [30]
Violence experience and use between adolescent peers	Adapted from ICAST-CI [30]
Violence from caregivers against adolescents’	Adapted from ICAST-CI [30]
Violence from work employers against adolescents’	Adapted from ICAST-CI [30]
Adolescent Intimate Partner Violence (IPV) experience and use	Adapted from the WHO Multi-Country study on women’s health and domestic violence against women [31], and the CADRI-Conflict in Adolescent Dating Relationships Inventory [32, 33]
Student attitudes towards teacher violence	Good Schools Study [34]
Adolescents attitudes towards gender equality and violence	Gender Equitable Men scale, Uganda version [35]
Mental health measures	Strengths and Difficulties Questionnaire (SDQ-25) [36, 37] Patient Health Questionnaire-Adolescent (PHQ-A) [38]

### Qualitative research instruments

Our ethnographic, participatory research design involves flexibility in the research methods, with some methods developed through negotiation with young people themselves, in order to ensure that the design is contextually relevant and sensitive to their concerns. Data will be collected through informal observations, with the researchers spending extended time in the communities, and gathering information through informal, unstructured ‘interview-conversations’ with the core participants, often together with their peers. Field diaries, completed on a daily basis, will record these. With core participants we will conduct semi-structured biographic narrative interviews, using a topic guide. The topic guide may be modified during researcher training and fieldwork team meetings, as further themes emerge as relevant for inclusion, and so that the research team can refine and practise sensitive ways to elicit personal data (for example, about violence and dating relationships). Topic guides will also be used to facilitate interviews and focus groups with parents, peers and other adults. We will also explore a range of participatory methods, including engaging young people as co-researchers, arts/drama based work, often together with peers, and photovoice. These have proved effective in creating a relaxed atmosphere for discussing sensitive topics with children and adolescents, in helping to avoid research fatigue, and eroding power imbalances in the research relationship. These approaches will be discussed and agreed with young people. We will also consult with our partners at Raising Voices, who have expertise in working with young people in this context, as well as with our youth advisors, to ensure the qualitative methods and instruments have contextual relevance, sensitivity and appropriateness for engaging young people in Luwero.

### Statistical power

We are powered to test our main hypothesis, 2.1, whether Wave 1 levels of exposure to violence (as an example, with 25% exposed to severe violence) are associated with Wave 3 past year experience of physical, sexual and/or emotional intimate partner violence. A conservative sample size of 2406 participants (allowing for 30% loss to follow up over the study) would give us 80% power at a 5% level of significance to detect an effect difference of 7–8% between exposed and non-exposed adolescents. This assumes that 70% will have had a relationship by Wave 3 and 25% of those unexposed to severe violence at Wave 1 had past year intimate partner violence at Wave 3, which would be expected based on 2012 Uganda DHS data about relationship prevalence and intimate partner violence [39]. Analyses involving mediators and moderators are exploratory and hypothesis generating. Power calculations for these depend on a large number of factors, most of which, as is common, are unknown at this stage of the study. Fritz and MacKinnon show that a sample size of 667 provides at least 80% power to detect mediation under a range of scenarios and different tests [40]. The 7–8% difference (equivalent to an odds ratio of about 1.3 in our sample) in adult IPV prevalence between those exposed and unexposed to childhood violence that we are powered to detect is in the range of what other studies have found, for example, Widom et al. [2] show an odds ratio of 1.6. However, we have been more conservative as we expect a slightly smaller difference between groups, because baseline levels of violence exposure are higher in our study.

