### Wave 2 inclusion criteria

#### Quantitative study

Of the 3820 pupils recruited at Wave 1, 3431 (90%) agreed to be re-contacted. These pupils are the eligible sample for Wave 2 and Wave 3. Participants must be deemed able to understand survey consent procedures in English or Luganda by interviewers, so that they can give voluntary informed consent. These adolescents will be our ‘index’ participants. Other participants will be sampled in connection with the index participant. A subsample of peers, intimate partners, and caregivers identified by each index participant will also be invited to participate in a face to face survey (n = approximately 200 of each in total).

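### The detectable 7–8 point difference is given as an odds ratio of about 1.3; at the plan's own 25% base rate it is 1.41–1.48, and 1.28–1.32 is the risk ratio

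*Protocol article*

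**What the plan says.** All the relevant statements are in the protocol article, section Statistical power, unless noted.

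- Sample: "A conservative sample size of 2406 participants (allowing for 30% loss to follow up over the study"). Under Wave 2 inclusion criteria, Quantitative study, the source cohort is given: "Of the 3820 pupils recruited at Wave 1, 3431 (90%) agreed to be re-contacted".
- Exposure split: "as an example, with 25% exposed to severe violence".
- Analysable share: "This assumes that 70% will have had a relationship by Wave 3".
- Base rate: "25% of those unexposed to severe violence at Wave 1 had past year intimate partner violence at Wave 3".
- Claim: "80% power at a 5% level of significance to detect an effect difference of 7–8% between exposed and non-exposed adolescents".
- Translation to a relative effect: "The 7–8% difference (equivalent to an odds ratio of about 1.3 in our sample").
- Benchmark: an earlier study is cited, said to "show an odds ratio of 1.6", and the authors describe their own target as the more conservative of the two.

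No other base rate for past-year intimate partner violence is given for this conversion.

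**The concern.** A difference between two proportions, together with one of the proportions, fixes the odds ratio. The paragraph supplies both, and the odds ratio they imply is not 1.3. The value 1.3 is what the risk ratio comes to.

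This is the only relative effect size offered for the main quantitative hypothesis, and the text uses it in an argument by setting it beside a published odds ratio. Someone reading the section would take it that an odds ratio of 1.3 is detectable with 80% power and that the target lies 0.3 below the benchmark. Neither follows from the stated inputs.

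**Working it through.** **Inputs.** From Statistical power: 2406 followed up, 70% with a relationship, 25% exposed, 25% outcome rate in the unexposed, 80% power, 5% significance. Assumption: the test is two-sided, since sidedness is not stated. No intraclass correlation or design effect is given, so the base case has none.

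**Step 1: the plan's own power figure.**
- Analysable: 2406 × 0.70 = 1684, of whom 0.25 × 1684 = 421 are exposed and 1263 unexposed.
- Power = Φ[(d − 1.96·SE0)/SE1], where SE0 uses the pooled proportion and SE1 the separate proportions.
- At d = 0.07: pooled proportion 0.2675, SE0 = 0.02491, SE1 = 0.02579. (0.07 − 1.96 × 0.02491)/0.02579 = 0.82, so power is 79.4%.
- At d = 0.08, power is 88.4%.
- Power of 80% is reached at d = 7.05 points. With an assumed design effect of 1.3 it is reached at 8.08 points.

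The claim of 80% power for 7–8 points reproduces.

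**Step 2: the conversion.** OR = [p1/(1 − p1)] / [p0/(1 − p0)] and RR = p1/p0, with p0 = 0.25, so p0/(1 − p0) = 0.3333.

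| Difference | p1 | Odds ratio | Risk ratio |
|---|---|---|---|
| 7 points | 0.320 | 0.4706/0.3333 = 1.41 | 1.28 |
| 7.5 points | 0.325 | 0.4815/0.3333 = 1.44 | 1.30 |
| 8 points | 0.330 | 0.4925/0.3333 = 1.48 | 1.32 |

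The stated 1.3 equals the risk ratio at the midpoint and matches none of the odds ratios.

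**Step 3: other readings of the 25%.**
- As the rate in the exposed: odds ratio 1.52–1.63.
- As the overall rate: 1.43–1.50.
- Spread over everyone, partnered or not (0.70 × 25% = 17.5%): 1.53–1.61.

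Each reading moves further from 1.3.

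**Step 4: the comparison with 1.6.**
- On the odds-ratio scale the gap is 1.6 − 1.48 = 0.12 to 1.6 − 1.41 = 0.19. The text implies 1.6 − 1.3 = 0.3.
- In points, an odds ratio of 1.6 on a 25% base gives p1 = 0.25 × 1.6/(1 + 0.25 × 0.6) = 0.348. That is 9.8 points, or a risk ratio of 1.39.

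**Step 5: power if the true odds ratio is 1.3.**
- p1 = 0.25 × 1.3/(1 + 0.25 × 0.3) = 0.3023, a difference of 5.2 points.
- With 421 and 1263: SE0 = 0.02478, SE1 = 0.02548. (0.0523 − 1.96 × 0.02478)/0.02548 = 0.15, so power is 56%.
- With an assumed design effect of 1.2, power is 49%. Over 1.1 to 1.3 it runs from 52% to 46%.

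**The case against.** The case for leaving the paragraph alone has weight. The operative statement is the one in percentage points, and it is correct. The odds ratio is a parenthetical gloss, not an input, and the cohort is already fixed at the 3431 who agreed to re-contact, so no recruitment decision turns on it. The two conclusions drawn from it also survive: 1.41–1.48 is still below 1.6, and it lies nearer to the published value, so the remark that the target is in the range of earlier findings is if anything better supported. All of this stands, and it limits the severity.

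It can also be said that an odds ratio of about 1.3 is not impossible for such a difference. The smallest odds ratio that a 7-point difference can have is ((1 + 0.07)/(1 − 0.07))² = 1.32, when the two rates straddle 50%, and that rounds to 1.3. For 8 points the minimum is 1.38. This does not rescue the statement, because the plan fixes the unexposed rate at 25%.

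A reader might infer more than the documents support:

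- That the study is underpowered or the sample size wrong. It is not: the power claim reproduces.
- That the error falls on the scale the final model will report. Quantitative data analysis specifies mixed regression models allowing for clustering by school, but names neither a link function nor an effect measure.
- That a null result will be taken to exclude an odds ratio of 1.3. Nothing in the article says results will be judged against this figure.
- That the authors mistook a risk ratio for an odds ratio. The numerical match makes this plausible, but the article does not show how 1.3 was obtained.

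**Conclusion.** The parenthetical odds ratio is wrong on the plan's own figures. At 25% in the unexposed, a 7–8 point difference is an odds ratio of 1.41–1.48, and 1.3 describes the risk ratio. This conversion rests only on the stated 25% and 7–8 points.

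The margin below the cited 1.6 is overstated: 0.12–0.19 rather than 0.3. The direction of the comparison holds. Under the stated inputs, a two-sided test and no clustering, power for a true odds ratio of 1.3 is about 56%. Any lower figure depends on a design effect that the article does not give.

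Severity is minor to moderate: a misreported sensitivity figure for the main hypothesis, with no consequence for the sample size or design.

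**What to change.** In Statistical power, replace the parenthetical with: odds ratio of about 1.4–1.5 (risk ratio about 1.3). Then restate the comparison with the published 1.6 on the odds-ratio scale, so that the margin reads as about 0.1–0.2.

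If power for an odds ratio of 1.3 is mentioned at all, give about 56% under the stated inputs without clustering. Label any lower value, such as 49% at a design effect of 1.2, as resting on an assumed design effect.

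The cost is a sentence or two of text. The stated sensitivity looks slightly less favourable; no participants are added and no analysis changes.

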### Quantitative data analysis

Descriptive analysis will be conducted at each Wave. We will use latent class analysis to explore patterns of violence at Waves 1,2 and 3 and regression analysis to subsequently explore whether the patterns/groupings persist over time. Mixed regression models, allowing for clustering by school will be used to explore whether experience of intimate partner violence at Wave 3 differs by Wave 1 and Wave 2 violence exposure group. The models will include the exposure measured at both Wave 1 and 2 where available and will be adjusted for pre-specified potential confounders. Finally, further regression analysis and structural equation models will be used to explore whether individual and contextual factors mediate or moderate the relationship between early exposures and later use and experience of violence. All analysis will include information on degree to which the participant was exposed to the Good School Toolkit intervention.

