This will be a mixed methods study with quantitative and qualitative research components, with a third stream of work where emerging research results are input directly into ongoing intervention development. Specifically, we will use quantitative survey data at 3 time points and qualitative data at 5 time points to: 1) examine the epidemiology and patterns of violence exposure in early adolescence; 2) understand which patterns of early adolescent exposure to violence are associated with violence use and experience in later adolescence and young adulthood; 3) explore the pathways by which violence in early adolescence, later adolescence and young adulthood are associated and how context encourages or interrupts these associations. Our overarching *hypothesis* is that context matters in shaping whether and how early violence exposure leads to later violence use and experience. Specific aims and hypotheses are outlined below.

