## Methods

The research will use quantitative data collected in 2014 for the Good Schools Study (Wave 1 survey) as the baseline for a prospective cohort, with follow-up surveys in 2018 (Wave 2) and 2021 (Wave 3). The Wave 1 survey data will also be used to select participants for the qualitative research, who will be followed at 4 additional time points (Fig. 3).

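### The only model described for Wave 3 intimate partner violence enters Wave 1 and Wave 2 exposure together, so its Wave 1 term is not the overall association that main hypothesis 2.1 states and the power calculation assumes

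*Protocol article*

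**What the plan says.** Under Aims and hypotheses, Aim 2 is labelled the main quantitative aim. Its hypothesis 2.1 is that use and experience of IPV at Wave 3 will differ between Wave 1 exposure groups. Wave 2 does not appear in it.

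Statistical power takes the same contrast, with IPV as the outcome: "whether Wave 1 levels of exposure to violence (as an example, with 25% exposed to severe violence) are associated with Wave 3 past year experience". The sample is described as "A conservative sample size of 2406 participants (allowing for 30% loss to follow up over the study"). The target is 80% power at the 5% level for a difference of 7–8 points between exposed and unexposed. The section also states: "Analyses involving mediators and moderators are exploratory and hypothesis generating".

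Quantitative data analysis describes mixed models, allowing for clustering by school, to explore whether "experience of intimate partner violence at Wave 3 differs by Wave 1 and Wave 2 violence exposure group". It then specifies the terms: "The models will include the exposure measured at both Wave 1 and 2 where available and will be adjusted for pre-specified potential confounders". No model with Wave 1 exposure alone is described. Mediation is left to a later step using further regression and structural equation models.

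Three other statements place Wave 2 violence between exposure and outcome. Hypothesis 1.2 predicts that Wave 1 patterns persist at Waves 2 and 3. The study sets out to "explore the pathways by which violence in early adolescence, later adolescence and young adulthood are associated". The 2014 survey is the baseline, "with follow-up surveys in 2018 (Wave 2) and 2021 (Wave 3").

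**The concern.** A regression with both exposure terms holds Wave 2 violence fixed when it estimates the Wave 1 coefficient. If early violence makes later-adolescent violence more likely, and that in turn makes Wave 3 IPV more likely, this adjustment removes a share of the association that 2.1 asks about. On the protocol's own hypotheses, the more strongly Wave 1 patterns persist, the smaller the Wave 1 coefficient becomes.

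A small or null Wave 1 coefficient from the joint model could then be read as evidence against 2.1 when it only shows that much of the association runs through continued exposure. The planned power would not apply to that coefficient either, because it was worked out for the unadjusted contrast. The protocol calls mediator analyses exploratory, yet the model described for the main outcome already conditions on a likely intermediate.

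**Working it through.** **1. Reproduce the plan's figure.** Inputs from Statistical power: 2406 participants, 70% with a relationship, 25% exposed, 25% IPV in the unexposed. A two-sided 5% level is assumed.

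- Analysed: 0.70 × 2406 = 1684, that is 421 exposed and 1263 unexposed.
- For a 7-point difference, p0 = 0.25, p1 = 0.32, pooled p = 0.75 × 0.25 + 0.25 × 0.32 = 0.2675.
- SE under the null = √[0.2675 × 0.7325 × (1/1263 + 1/421)] = 0.0249.
- SE under the alternative = √[0.25 × 0.75/1263 + 0.32 × 0.68/421] = 0.0258.
- z = (0.07 − 1.96 × 0.0249)/0.0258 = 0.82, so power is 79.4%.
- For 8 points, power is 88.4%. The detectable difference at 80% power is 7.05 points.

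The stated figure therefore reproduces as a comparison of Wave 1 groups with no Wave 2 term and no allowance for clustering. It is power for the total association.

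**2. What the Wave 2 term does to the coefficient.** Let q1 and q0 be the proportions with severe violence at Wave 2 among the Wave 1 exposed and unexposed, and b the risk difference in Wave 3 IPV for Wave 2 violence. With additive risks and no interaction:

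coefficient left for Wave 1 = total difference − b × (q1 − q0).

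If b and q1 − q0 are both positive, the coefficient is below the total. The documents give neither quantity, so the values below are assumptions.

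- Weak persistence: q1 = 30%, q0 = 20%, b = 5 points. Removed: 0.05 × 0.10 = 0.5 points, so 7 becomes 6.5 and 8 becomes 7.5.
- Stronger persistence: q1 = 45%, q0 = 18%, with a quarter, a third or half of the association running through Wave 2. For half, 7 becomes 3.5 and 8 becomes 4. The implied b is 0.035/0.27 = 13.0 points or 0.04/0.27 = 14.8 points.

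**3. Power for the Wave 1 term.** Cell risks are a + d × W1 + b × W2, with d the coefficient left and a = 0.25 − b × q0. A logistic model is fitted to the expected counts for 1684 participants, and power = Φ(log OR/SE − 1.96).

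| Model and assumption | Wave 1 OR (7 to 8 points) | Power (7 to 8 points) |
|---|---|---|
| Wave 1 only | 1.41 to 1.48 | 80% to 89% |
| Plus Wave 2: 30% vs 20%, b = 5 points | 1.38 to 1.44 | 73% to 85% |
| Plus Wave 2: 45% vs 18%, a quarter via Wave 2 | 1.30 to 1.34 | 52% to 63% |
| Plus Wave 2: 45% vs 18%, a third via Wave 2 | 1.26 to 1.30 | 43% to 53% |
| Plus Wave 2: 45% vs 18%, half via Wave 2 | 1.19 to 1.22 | 27% to 34% |

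The Wave 1-only row differs slightly from step 1 because it uses the logistic Wald test instead of the pooled test of proportions.

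The loss comes from the smaller coefficient and hardly at all from collinearity. The squared correlation of the two exposures is 0.011 in the weak case and 0.073 in the stronger ones, which widens the standard error by factors of 1/√(1 − 0.011) = 1.005 and 1/√(1 − 0.073) = 1.04.

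**The case against.** **The text never says which coefficient tests 2.1.** The analysis paragraph does not name the hypothesis, uses the plural for its models, and could describe a comparison of joint exposure histories. A two-degree-of-freedom test of both exposures would not lose power: with 45% versus 18% at Wave 2, a 7.25-point total difference and a quarter of it through Wave 2, it rejects about 94% of the time. This stands in part. The loss belongs to the Wave 1 term and not to every use of the model. But the joint test can be positive because of Wave 2 violence alone, so it does not test 2.1 either. The article also does not leave the terms open: it names them, and no Wave 1-only model appears.

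**A reader might infer that the main test necessarily loses its 80% power.** The documents do not support that. Under weak persistence and an 8-point difference, power for the Wave 1 term is still about 85%. Nor is the direction guaranteed: common causes of Wave 2 violence and Wave 3 IPV can bias the conditional coefficient further, in a direction that cannot be fixed from the documents.

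**A reader might infer that the qualifier about availability means participants missed at Wave 2 are dropped or modelled differently.** The text does not say so. The phrase more naturally refers to exposures measured at both waves, since the Wave 2 questionnaire combines Wave 1 items with measures from other sources.

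**Joint modelling is legitimate.** It is, for the effect of Wave 2 exposure given Wave 1 or for the part of the association not explained by continued violence. Those are different questions from 2.1.

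**Conclusion.** The concern holds as a mismatch between the main hypothesis and the model described. Hypothesis 2.1 and the power statement are about the total Wave 1 association. The Wave 1 term in the stated model is a conditional one, given Wave 2 violence. That follows from the stated terms and the order of the waves, without numerical assumptions. That the coefficient is generally smaller rests on positive persistence and a positive link from Wave 2 violence to IPV, both of which the protocol anticipates.

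The size is uncertain. For total differences of 7–8 points, power for the Wave 1 term runs from about 73–85% to about 27–34% over the assumptions shown, against 80–89% without the Wave 2 term. The Wave 2 prevalences, the Wave 2 effect and the mediated shares are all assumed, risks are taken as additive, and clustering is ignored throughout. It should be settled before the Wave 3 analysis because it decides what the main result means.

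**What to change.** State in Quantitative data analysis that hypothesis 2.1 is tested in a mixed model with Wave 1 exposure group and confounders that are not affected by Wave 1 exposure and were measured at or before Wave 1, without Wave 2 exposure. The confounders should not be described as pre-exposure merely because they come from Wave 1: that survey is the cohort baseline and records violence that has already happened, so its covariates are concurrent with exposure and each needs a reason for being treated as unaffected by it.

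Keep the joint Wave 1 and Wave 2 model as a secondary analysis, labelled either as the effect of Wave 2 exposure or, under Aim 3, as the association not explained by continued exposure.

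The cost is one sentence and one extra model. No new data are needed and the sample size is unchanged.
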